## Abstract

**Background:**

Malignant neoplasms are among the most common causes of disease-related death in children. Long-term chemotherapy often requires a high degree of parental involvement. Family caregivers’ preparedness and capacity are critical in reducing the burden of care and improving quality of life. This study looks to examine the impact of a family-centered empowerment model (FCEM)–based intervention on the caregiving capacity and preparedness of family caregivers.

**Objective:**

This study aims to develop and evaluate an FCEM-based intervention to improve caregiving preparedness and capacity among family caregivers of children with malignant neoplasms. It also examines the potential effects of the intervention on self-efficacy and psychological outcomes, including depression, anxiety, and stress.

**Methods:**

This quasi-experimental study focuses on caregivers of children with malignant neoplasms attending our hospital for the first time, implementing a 4-phase FCEM-based intervention program evaluated through questionnaires administered 3 days after admission and 3 days before discharge. Differences in caregiving preparedness, caregiving capacity, self-efficacy, and depression, anxiety, and stress scores will be assessed using independent and paired *t* tests, Mann-Whitney tests, and paired rank-sum tests for both within-group and between-group comparisons preintervention and postintervention.

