## Methods

### Data Collection

#### Setting and Participants

This is a quasi-experimental study. This protocol is version 1.0, finalized on July 8, 2025. We will select children with malignant tumors and their family caregivers who were hospitalized at West China Second Hospital, Sichuan University, between July 2025 and December 2026. Family caregivers of the children will be enrolled. The researchers will provide a detailed description of the study’s purpose and content to the participants, who must sign an informed consent form.

The QR code for the web-based questionnaire will be distributed after caregivers provide informed consent. The family caregivers recruited for the study will be divided into control and intervention groups. Children will be grouped according to their diagnosis and treatment timeline as follows: children admitted from July to December 2025 will form the control group, and those admitted from July to December 2026 will form the intervention group. The caregivers of the children will be enrolled along with the children. In the intervention group, the intervention program will be implemented after inclusion. For the control group, where routine health promotion is implemented, an intervention program based on FCEM will be offered upon the second admission to the hospital (Figure 1).

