**Figure 1 figure1:**
[figure not shown]
Participant timeline.

After the family caregivers complete the baseline survey, the researchers will distribute paperwork or provide verbal health promotion with relevant health promotion components and assess the caregivers’ knowledge weekly.

The questionnaire will be re-administered 3 days before the child is discharged. One researcher will enter the data, which will be double-checked for errors by another researcher. After all data are entered, the analysis will be performed by a designated specialist who remains unaware of the groupings. Finally, 2 additional researchers will independently review the analyses to ensure accuracy. Family caregivers will be aware of their grouping. If family caregivers prefer to adjust their groupings, appropriate adjustments will be made based on their identified needs.

The inclusion criteria are as follows: (1) children aged 0-18 years, (2) children clinically diagnosed with malignant neoplasms, and (3) first-time visitors to our hospital.

The exclusion criteria are as follows: (1) children diagnosed and treated with radiotherapy or chemotherapy in other hospitals and (2) children undergoing their first treatment in our hospital for recurrence of the disease.

Primary caregiver inclusion criteria are as follows: (1) the caregiver is enrolled along with the child, (2) the caregiver is aged 18 years or older, (3) the caregiver is a member of the child’s immediate family, (4) the caregiver has cared for the child for the longest period among multiple caregivers, (5) the caregiver has basic communication and reading skills and is proficient in Chinese, and (6) the caregiver has no previous history of psychiatric illness or consciousness-related disorders.

The sample size was calculated to be 128 using G*POWER 3 software [10] with the parameters α=.05, 1 – β=0.8, and effect size=0.5. Considering a 10% lost-to-follow-up rate, the total sample size required was estimated to be 142, with 71 caregivers in the intervention group and 71 in the control group.

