#### Intervention Delivery Process

##### Intervention Group

The intervention group will be provided with a family empowerment intervention program based on usual care.

Three sessions of approximately 15-30 minutes each will be conducted within 3 days of the child’s admission to the hospital, from the fourth day to 3 days before discharge. The timing of the intervention sessions was determined based on evidence from a prior study conducted in China involving caregivers of children with asthma combined with clinical experience [19]. The researcher or charge nurse will assess the caregivers’ knowledge every week using uniform evaluation criteria and adjust the topic or number of interventions within each phase based on the knowledge gained, with the final intervention content and timeline remaining unchanged.

During stage 1 (within 3 days of admission), the researchers will explain the use of the facilities in the ward, including the proper use of a hospital bed or laminar flow bed, and outline safety precautions in the ward (including preventing falls, falls out of bed, and avoiding burns). They will also provide information about daily care, infection prevention, dietary considerations (eg, low-fat diets and special diets for children experiencing vomiting), input and output monitoring, the recognition of symptoms for oral and perianal infections and how to gargle and cleanse the perianal area, and disease-related information, including cure rates and recurrence rates. Completing stage 1 will require 15-25 minutes.

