During stage 2 (fourth day after admission to 3 days before discharge) the nurse in charge will ask the main caregiver about difficulties and problems encountered during the caregiving process using open-ended questions, such as “In your opinion, what is the most difficult thing right now?” “Do you have difficulties taking care of your children and yourself?” “What kind of information would you like the nurse to provide more of while providing care for your child?” Based on the preinterview, the nurse will conduct adequate communication with the main caregiver in response to their difficulties, listen patiently, and provide positive guidance tailored to their psychological state. A childcare program will be developed, and the following content will be explained to the patient’s family, part of which will be presented in written or video form: (1) medication guidance based on the actual use of drugs by the child, including the dosage, frequency, and adverse effects of the drugs; (2) PICC-related knowledge, including daily observation, handling of abnormalities, prevention and identification of complications, and precautions for daily life and exercise; (3) postoperative care for infusion port implantation, including postoperative diet, postoperative medication changes, observation during use, and postdischarge precautions; (4) blood indicators, including an explanation of blood indicators, such as platelets, hemoglobin, and neutrophils, along with precautions to be taken in case of critical values; (5) condition monitoring and emergency treatment, including simple treatments in case of fever or other emergencies; and (6) psychological support, including sharing stories of other successful cases to positively motivate the caregivers. Completing stage 2 will require 20-30 minutes.

Stage 3 (3 days before discharge) will involve the evaluation of outcomes and discharge instructions as well as communication with the patient to address problems related to caregiving abilities and caregiving preparedness, affirm the level of care provided by the family caregiver during the child’s hospitalization, boost their confidence, and guide the child’s postdischarge medication, nursing care, review, and follow-up chemotherapy plans. Completing stage 3 will require 10-20 minutes.

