Stage 4 encompasses the entire implementation process. During program implementation, a dedicated researcher will coach the primary caregiver 1-on-1 to ensure they understand the program content (ie, until they can repeat it independently). Family caregivers will be instructed to record changes in their children’s symptoms. The family caregivers’ knowledge of the program will be assessed weekly (Multimedia Appendix 2).

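### The stated assessment days do not guarantee that the two in-hospital questionnaires bracket the intervention

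*Protocol article*

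**What the plan says.** **Baseline.** The Abstract (Methods) has the programme "evaluated through questionnaires administered 3 days after admission and 3 days before discharge". No other section repeats the day-3 figure. In Setting and Participants, the questionnaire's QR code goes out once consent is given, and "In the intervention group, the intervention program will be implemented after inclusion". The text after Figure 1 then gives an order: "After the family caregivers complete the baseline survey, the researchers will distribute paperwork or provide verbal health promotion".

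**Stage 1.** The Intervention Group section reads "During stage 1 (within 3 days of admission), the researchers will explain the use of the facilities in the ward". It goes on to daily care, infection prevention, diet, symptom recognition and disease information.

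**Post-test and Stage 3.** Setting and Participants says "The questionnaire will be re-administered 3 days before the child is discharged". The Intervention Group section says "Stage 3 (3 days before discharge) will involve the evaluation of outcomes and discharge instructions". Stage 3 also takes up problems with caregiving ability and preparedness, affirms the caregiver and builds confidence. Coaching and weekly knowledge checks run throughout: "Stage 4 encompasses the entire implementation process".

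**Later assessment.** Follow-Up Assessment repeats the same instruments 1 month after discharge. Data Analysis does not name this time point.

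**Analysis.** Data Analysis compares the groups before the intervention by independent *t* tests. It then tests within-group and between-group differences after the intervention. The second research hypothesis is a change from earlier measurements within the intervention group.

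**The concern.** The analysis takes for granted that one questionnaire precedes the intervention and the other follows it. The stated days do not secure either.

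A baseline completed after Stage 1 already holds part of any benefit from that stage. The paired change in the intervention group, which is what the second hypothesis tests, would then probably be too small. The baseline comparison would also be contaminated. That matters more here than in a randomised trial: the groups are admission cohorts a year apart, and this comparison is an important check that they are alike.

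A post-test completed before Stage 3 leaves that component unmeasured. Completed just after Stage 3, it records the response to the whole in-hospital programme, but very close to a conversation about preparedness and confidence, from caregivers who know their group. A measurement taken at the wrong time cannot be corrected afterwards.

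**Working it through.** **1. The plan's own sample size.** Inputs from Setting and Participants: α = 0.05, power 0.8, effect size 0.5, 10% loss. A two-sided, two-sample *t* test (noncentral *t*) gives 63.77, so 64 per arm and 128 in total, as stated. A one-sided test would need 51 per arm and does not match. Allowing for loss, 128 / 0.9 = 142.2, stated as 142 (71 per arm). The sample size is not in dispute; 64 per arm is used below.

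**2. The days laid side by side** (day 0 = admission, D = discharge).

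| Event | Stated time | Where |
|---|---|---|
| Stage 1 | up to day 3 | Intervention Group |
| Baseline | day 3 | Abstract |
| Baseline | before health promotion | Setting and Participants |
| Stage 2 | day 4 to D − 3 | Intervention Group |
| Stage 3 | D − 3 | Intervention Group |
| Post-test | D − 3 | Abstract; Setting and Participants |
| Follow-up | D + 1 month | Follow-Up Assessment |

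- Front end: the Abstract's baseline falls on the last day of the Stage 1 window, so Stage 1 may already be complete. Setting and Participants implies the opposite order. The statements agree only if Stage 1 is held on day 3 after the survey, or if the Abstract means within 3 days. The text says neither.
- Back end: the post-test and Stage 3 share a day, and no sentence puts one first.

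**3. What each ordering does.** Let the full programme effect be 0.5 SD (the planned value), with SD unchanged and the groups otherwise comparable. The fractions below are assumptions; the documents give none.

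*Baseline after Stage 1, with fraction g of the effect already present:*

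- spurious baseline difference = 0.5 × g
- intervention part of the paired change = 0.5 × (1 − g)
- unadjusted post-test difference = 0.5, whatever g is

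For g = 0.20 these are 0.10, 0.40 and 0.50 SD. For g = 0.50 they are 0.25, 0.25 and 0.50 SD. Power of the post-test comparison stays at 80.1% throughout.

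*Post-test before Stage 3, with fraction h of the effect not yet delivered:*

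- post-test difference = 0.5 × (1 − h), and the intervention part of the paired change shrinks in the same way
- power of the between-group test comes from the noncentral *t* with 126 degrees of freedom and noncentrality d × √(64/2)

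| h | difference (SD) | power, 64 per arm |
|---|---|---|
| 0 | 0.50 | 80.1% |
| 0.10 | 0.45 | 71.4% |
| 0.20 | 0.40 | 61.2% |
| 0.25 | 0.375 | 55.8% |
| 1/3 | 0.333 | 46.5% |
| 0.50 | 0.25 | 28.9% |

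*Post-test after Stage 3 on the same day:* h = 0. No component is missed, but the answer is an immediate one.

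**The case against.** The strongest reply is that this is an Abstract figure that fits poorly with the Methods, and that the Methods already have the right order. Much of that stands. Setting and Participants points to a survey before any health promotion, and a day-3 survey followed the same day by Stage 1 would satisfy every statement. Figure 1, the participant timeline, is not visible in the text reviewed and may show the order. A reader might infer that the baseline is definitely taken after Stage 1; the documents do not support that.

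Four further points stand, wholly or in part:

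- A post-test completed after the Stage 3 session on the same day is a post-intervention measurement. Affirmation is part of the programme, so responding to it is not bias in itself. What is missing is the stated order.
- The 1-month assessment follows all the in-hospital sessions, so a reader should not infer that nothing is measured after the intervention. It does not settle the matter, because the Abstract presents only the two in-hospital questionnaires as the evaluation and Data Analysis does not say which time point is meant by after.
- A reader might note that in a 6-day stay day 3 equals D − 3, so both questionnaires would coincide. The arithmetic is right, but the documents give no length of stay, and weekly knowledge checks suggest longer ones.
- A reader might quote power losses from a late baseline for a change-score comparison or ANCOVA. Data Analysis names neither explicitly, and the unadjusted post-test comparison loses nothing from a late baseline.

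**Conclusion.** The concern holds as an unresolved inconsistency at the front end and an unstated order at the back end. It does not hold as a proven failure to measure before and after.

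The front end puts at risk the paired change in the intervention group and the baseline comparability check. If Stage 1 helps and precedes the baseline, the first is probably understated and the second contaminated, by 0.10 SD for an assumed 20% share of a 0.5 SD effect. The between-group post-test comparison is untouched.

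The back end can affect both comparisons, but only if the post-test precedes Stage 3. Power is then 71.4% for an assumed 10% share of the effect in Stage 3 and 28.9% for 50%. These figures rest on the planned effect size, 64 analysed per arm, an unchanged SD and shares that the documents do not give, so they show a range and not an estimate. The remedy is nearly free, and it is best settled before the intervention wave opens in July 2026.

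**What to change.** Reconcile the Abstract, Setting and Participants (including the text after Figure 1) and the Intervention Group section by moving the questionnaires and leaving the sessions where they are.

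- **Baseline:** complete it at consent and before any Stage 1 content, with the same timing relative to admission in both waves.
- **Post-test:** keep it at discharge minus 3 days in both waves. In the intervention wave, complete it by self-administered web form after the Stage 3 session. Moving it to discharge day is not advised: the control wave is scheduled at discharge minus 3 days, so a later post-test in the intervention wave would confound assessment timing with arm.
- **Records:** log the date and time of each questionnaire and each stage, and flag any control data collected under a different timing.
- **Analysis text:** say which time point is meant by after, and state that the 1-month assessment is the one clear of all the in-hospital sessions. Controls are offered the programme at a second admission whose date is not given, so record whether the 1-month assessment comes before it.

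The cost is a wording change and minor scheduling work. One limitation remains: the post-test still follows Stage 3 closely, so it shows an early response, and only the 1-month assessment can show whether that response lasts.

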**Results:**

Recruitment will be conducted in 2 waves (control group: July to December 2025; intervention group: July to December 2026). It is expected that the intervention group will show significantly greater improvements in caregiving preparedness, caregiving capacity, and psychological well-being compared to the control group.

**Conclusions:**

The findings of this study are expected to provide evidence for the development of structured family empowerment in pediatric oncology. In the future, expanding to multiple centers and conducting targeted surveys among caregivers of children with different cancer types would help validate and promote the effectiveness of family empowerment interventions.

**Trial Registration:**

ClinicalTrials.gov NCT06810388; https://clinicaltrials.gov/study/NCT06810388

**International Registered Report Identifier (IRRID):**

PRR1-10.2196/73304

## Introduction

### Background

Malignant neoplasms in childhood usually refer to malignant tumors with onset between the ages of 0 and 14 years and are the most common cause of death from childhood illnesses, including leukemia, lymphomas, tumors of the brain and central nervous system, and osteosarcomas [1-3]. Approximately 13.7 million children younger than 15 years are predicted to suffer from tumors by 2050 [4]. In China, approximately 22,000 cases of malignant neoplasms occur in children younger than 15 years each year, and the prevalence rate is estimated to increase annually by 5% [4].

Family caregivers, often parents or grandparents, manage children’s daily needs, provide emotional support, and respond to sudden illnesses and other conditions. Since children are in a critical stage of growth and development, and their tumors are characterized by high malignancy, disease complexity, early onset, prolonged chemotherapy cycles, and numerous adverse reactions, family caregivers must provide extensive care. Their preparedness and capacity play pivotal roles in reducing caregiving burdens and enhancing quality of life [4-6].

The family-centered empowerment model (FCEM), developed by Alhani et al [6] in 2003, aims to empower patients and their families by defining essential elements for improving chronic care outcomes [6]. This model builds on the family-centered care philosophy, which emphasizes the child’s family as the “center of capacity building” [6].

The FCEM involves a 4-step process. The first step consists of improving knowledge through educational programs using resources, such as posters, models, and handouts, as well as interactive methods, including quizzes and question-and-answer sessions. The second step is self-efficacy enhancement, the third step is the promotion of self-esteem through participation in educational activities, and the fourth step involves evaluating the entire intervention period [6]. By following this structure, FCEM helps caregivers acquire the necessary skills and confidence to manage their child’s condition effectively and maintain a balanced family life [6].

This model has also been widely used for patients with chronic diseases in China. Nonpharmacologic interventions based on the FCEM have demonstrated positive effects on the quality of life, knowledge, and self-efficacy of patients with chronic diseases, such as chronic obstructive pulmonary disease, thalassemia major, asthma, and myocardial infarction. These interventions also alleviate stress, anxiety, and restlessness in family caregivers [7,8]. While FCEM was initially developed for chronic illnesses, its structured framework is equally applicable to the caregiving needs of family caregivers of patients with malignant tumors [9].

Although studies highlight the positive impact of FCEM-based interventions on caregivers of patients with malignant neoplasms [7-9], most have focused on primary caregivers of adult patients. Compared with adults, children require more detailed and comprehensive care because of their younger age, longer chemotherapy cycles, and critical developmental stages. This necessitates caregivers with greater preparedness and advanced caregiving skills. The impact of the FCEM on caregiving capacity and preparedness among family caregivers of children with malignant neoplasms remains unclear.

### Objectives

This study aims to recruit family caregivers of children with malignant neoplasms to develop a corresponding intervention program based on the FCEM and to evaluate its impact on caregiving preparedness and caregiving capacity. Additionally, the study aims to examine the effects of the empowerment intervention on caregivers’ self-efficacy as well as their levels of depression, anxiety, and stress.

### Research Hypotheses

This study has the following research hypotheses:

Statistically significant differences in caregiver preparedness and caregiving capacity will occur after the FCEM intervention program.Significant differences in self-efficacy, depression, anxiety, and stress will occur in the intervention group after the intervention compared to previous measurements.

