### Data Analysis

Data will be analyzed using SPSS version 26.0 (IBM Corporation). For general information, measurement data conforming to a normal distribution will be described by means and SDs, and count data will be described by frequencies and constitutive ratios. Missing data will be removed and will not be included in the analysis. Participants who request to switch groups based on their preferences will be excluded from the primary analysis; however, we will summarize the baseline characteristics of these participants and compare them to those who remain in their originally assigned groups. This comparison will include demographics to assess the potential impact of nonrandom attrition on study validity.

Independent-sample *t* tests will be used to compare caregiving preparedness, caregiving capacity, self-efficacy, and depression, anxiety, and stress scores between the 2 groups before the intervention. After the intervention, both within-group and between-group differences in these variables will be analyzed using independent-sample *t* tests, paired *t* tests, Mann-Whitney tests, and paired rank-sum tests.

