### Self-Efficacy Outcomes

Regarding the self-efficacy outcomes, caregivers receiving the intervention are likely to show increased self-efficacy after discharge. No major change is expected in the control group.

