### Psychological Outcomes

Caregivers in the intervention group are expected to report significantly lower depression, anxiety, and stress scores after the intervention.

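### Hypothesis 2 defines success for self-efficacy, depression, anxiety and stress as a pre-post change in the intervention group, and the planned between-group test is not made to decide it

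*Protocol article*

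**What the plan says.** The Objectives section sets a causal aim: "the study aims to examine the effects of the empowerment intervention on caregivers’ self-efficacy as well as their levels of depression, anxiety, and stress". The Research Hypotheses section turns this into a one-group contrast: "Significant differences in self-efficacy, depression, anxiety, and stress will occur in the intervention group after the intervention compared to previous measurements". The control group is not mentioned in that hypothesis.

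Two passages on expected results bear on the same outcomes. Under Psychological Outcomes: "Caregivers in the intervention group are expected to report significantly lower depression, anxiety, and stress scores after the intervention", again with no comparator. Under Self-Efficacy Outcomes, an increase is expected in the intervention group, followed by: "No major change is expected in the control group".

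The analysis text is broader. At baseline, independent-sample *t* tests will "compare caregiving preparedness, caregiving capacity, self-efficacy, and depression, anxiety, and stress scores between the 2 groups before the intervention". For the second assessment, the Data Analysis section states that "both within-group and between-group differences in these variables will be analyzed using independent-sample" and paired *t* tests and their rank-based counterparts. The Methods paragraph of the Abstract likewise lists the tests "for both within-group and between-group comparisons preintervention and postintervention". The Results paragraph of the Abstract expects psychological well-being to improve more in the intervention group than in the control group; it does not name self-efficacy.

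**The concern.** A before-after change in one group combines any effect of the programme with whatever would have happened anyway. Here the caregivers are those of children on a first visit to the hospital. The first questionnaire comes 3 days after admission and the second 3 days before discharge. Some adaptation over that interval is plausible without the programme, particularly as routine care already includes education, staff support and communication.

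The same scales are completed by a control group, so the study can separate common change from an intervention effect. The hypothesis does not ask it to. If the paired test were significant and the between-group test were not, hypothesis 2 as written would still count as supported. Readers would then take a finding on four outcomes as evidence for the programme when the controlled comparison had not shown it.

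**Working it through.** **1. What the sample size was built for.** Inputs from Setting and Participants: α = 0.05, power 0.80, effect size 0.5, 10% loss to follow-up, 71 per group.

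- Two-sample *t* test, two-sided, noncentral *t* with noncentrality 0.5 × √(n/2): the smallest n reaching 0.80 is 64 per group, power 0.801, total 128. This reproduces the stated 128.
- Loss to follow-up: 128 / 0.90 = 142.2, stated as 142 (71 per group).
- A paired test with a standardised mean change of 0.5 would need only 34 caregivers.

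The stated size is therefore that of a between-group comparison, which is not the contrast in hypothesis 2.

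**2. How often the hypothesis 2 contrast is significant with no intervention effect.** Assumptions, none of them given in the article:

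- a natural shift of d SD, equal in both groups;
- a pre-post correlation r;
- n = 64 in the intervention group (71 × 0.90 = 63.9);
- a two-sided 0.05 level;
- normally distributed scores.

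Standardised mean change: dz = d / √(2(1 − r)). Noncentrality: dz × √64 = 8 × dz, with 63 degrees of freedom. Example: d = 0.2 and r = 0.5 give dz = 0.2 / √1 = 0.2, noncentrality 1.6, and probability of significance 0.351.

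| Natural shift | r = 0.3 | r = 0.5 | r = 0.7 |
|---|---|---|---|
| 0 SD | 5% | 5% | 5% |
| 0.1 SD | 10% | 12% | 17% |
| 0.2 SD | 27% | 35% | 53% |
| 0.3 SD | 52% | 66% | 86% |

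With all 71 caregivers analysed, the figures are slightly higher: 29-57% at 0.2 SD and 56-90% at 0.3 SD.

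**3. The same scenario with the between-group test.** In 20,000 simulated trials per shift (n = 64 per group, r = 0.5, shifts of 0, 0.2, 0.3 and 0.5 SD in both groups), the two-sample test rejected in 4.8% to 5.1% of trials, whether applied to post scores or to change scores. The simulated paired test agreed with the formula (0.353 and 0.659 at 0.2 and 0.3 SD). Analysis of covariance was not simulated, but the reasoning carries over: a shift common to both groups goes into the intercept and leaves the group coefficient at zero.

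**4. Which test decides.** The hypothesis states a within-group change. The analysis text lists within-group and between-group tests side by side. The Abstract's expected result is a comparison with control. None of these says that the between-group result settles hypothesis 2.

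**The case against.** The best reply is that a controlled analysis is already planned. The Data Analysis section covers all these outcomes with between-group tests, the Abstract says the same, and the sample size is that of a between-group test. The four outcomes are also introduced as additional aims, and the choice of deciding test is often left to an analysis plan, which is not shown here.

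Much of this stands, and it rules out several stronger readings that a reader might infer:

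- **That these outcomes are tested only within the intervention group.** The article does not say so, and its analysis section says otherwise.
- **That efficacy will be claimed when one group changes significantly and the other does not.** The Self-Efficacy Outcomes text contrasts each group's own change, but as an expected result. No decision rule of that kind is stated, so an error rate for it would describe a procedure that is not planned.
- **That regression to the mean will produce the change.** No eligibility criterion selects caregivers on a distress or self-efficacy score. Natural adaptation is plausible; its size and direction are not given and may differ between scales.
- **That natural change would confirm the hypothesis.** It could. With a shift of 0.1 SD the chance is only 10-17%.

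The reply does not dispose of the wording. The hypothesis is not a detail left open for another document: the article states it, and states it without a comparator. An analysis plan that followed it faithfully would let the paired test decide.

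**Conclusion.** The point holds as a defect in how hypothesis 2 is stated and linked to the analysis; the controlled comparison itself is already planned. As written, the hypothesis can be supported with zero intervention effect, and so it does not answer the objective behind it.

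The size depends on two unknowns. For a natural shift of 0.2 to 0.3 SD and a correlation of 0.3 to 0.7, the paired test would be significant in roughly 27% to 86% of trials per outcome, against about 5% for the between-group test. These figures assume an equal shift in both groups and no difference between recruitment periods. The wording defect itself rests on the text alone and does not depend on them.

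**What to change.** - **Research Hypotheses:** restate hypothesis 2 as a difference between intervention and control in self-efficacy, depression, anxiety and stress at the post-intervention assessment, adjusted for the baseline score (for example by analysis of covariance).
- **Data Analysis:** name that contrast as the test that decides hypothesis 2, and label the within-group paired tests as descriptive.
- **Self-Efficacy Outcomes and Psychological Outcomes:** reword the expected results as comparisons with the control group, in line with the Abstract.

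The cost is a few sentences. The baseline and post scores are already collected in both groups, and 64 per group was sized for a between-group test. The downside is that fewer significant results may be reported. Recruitment of the intervention group is planned from July 2026, so a change made before then precedes any intervention data.

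One limit remains. The control group is an earlier, non-randomised cohort (admissions July to December 2025, against July to December 2026). The restated contrast removes natural change common to both groups, but not differences between the two periods, and the report should say so.
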